### Protocol amendments

The ethical committee will review all changes about the study protocol, which will be reported to the sponsor and investigators.

### Data monitoring

The data monitoring committee (DMC) consists of an independent researcher, who responsible for data collection and classification, and a statistician. The DMC will only perform data monitoring and not be included in the study. The baseline characteristics of individuals enrolled in the groups will be recorded. Monitoring will verify the completeness and accuracy of the data and assess the progress of the research. At the end of the trial, we will submit the original data and the final experimental dataset and consequences to the scientific research management committee.

### Safety evaluation

The researchers will monitor all adverse events (AEs) associated with the PEEP titration procedure. AEs are defined as hypotension, significant cardiac arrhythmias, pneumothorax, significant disability or incapacity, and even death. The researchers will visit all patients in the trial daily until they are discharged from the hospital and record the occurrence of all AEs in detail. Once AEs occur, the trial will be suspended and an investigation will begin.

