### Discharge criteria

The discharge criteria are as follows: (1) baseline rSO2 < 60%; (2) the operation time > 4 h, (3) intraoperative blood loss > 800 ml; (4) interruption of study protocol.

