### Interventions

Noninvasive blood pressure (NIBP), electrocardiogram, pulse oxygen saturation, bispectral index (BIS), body temperature, and rSO_2_ of patients in each group will be routinely monitored after entering the operating room. We will place two brain oxygen electrodes 4 cm from the forehead to the brow arch (one on the left and another on the right) to measure rSO_2_ by using near-infrared spectroscopy (NIRS). After placement of monitors, radial artery puncture and catheterization will be performed under local anesthesia, allowing intermittent blood gas analyses and continuous hemodynamic monitoring.

Patients will receive intravenous propofol (2 mg/kg), sufentanil (0.3 µg/kg), and cisatracurium (0.15 mg/kg) for anesthesia induction and tracheal intubation after preoxygenated (inspired oxygen fraction of 0.8) for three minutes. During surgery, sevoflurane inhalation and continuous intravenous remifentanil and propofol infusion will be employed to maintain BIS between 40 and 60. Intermittent administration of cis-atracurium will provide sufficient muscle relaxation. Vasoactive drugs will be used to maintain mean arterial pressure (MAP) and heart rate within ± 20% of the baseline. The core temperature will be maintained above 36.0 ℃ by using a forced air warming system. Subsequently, when patients can respond to verbal commands, they will undergo extubating procedures and be transferred to the postanesthesia care unit (PACU) until fully awake. Patients will routinely receive intravenous patient-controlled analgesia (PCIA) to control postoperative pain.

Mechanical ventilation will be maintained with V_T_ 6 ml/kg PBW, FIO_2_ of 50%, and I: E of 1:2 with PCV-VG mode. After the prone position is established, both groups will receive the recruitment maneuver by squeezing a reservoir bag up to 30–40 cm H_2_O for 15–20 s. The initial respiratory rate will be set to 12 breaths per minute and P_ET_CO_2_ is maintained in the range of 40 ± 5 mm Hg by adjusting the respiration rate.

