The patients in both groups will receive the PEEP of 5 cm H_2_O after endotracheal intubation, and this PEEP level will be maintained throughout the whole procedure in the group C. After the prone position is set up, patients in Group I will receive optimal individualized PEEP identified by an incremental PEEP titration protocol (Fig. 2). The PEEP titration method is as follows: each PEEP level (4, 6, 8, 10, 12, 14, 16 cm H_2_O) will be maintained for 60 s. Meanwhile, we will record the Cdyn at each PEEP level. We will select the optimal PEEP level based on the maximum Cdyn and maintain it throughout the whole study period. If circulatory instability occurs during PEEP titration, intravenous infusion of noradrenaline will be used to maintain MAP ≥ 55mmHg.

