### Statistical methods

SPSS (version 22.0, IBM) will be used for statistical analyses. The data with a normal distribution are expressed as mean ± standard deviation (SD) and compared by independent-samples t tests. The data of non-normally distribution are expressed as median (interquartile range) and compared by Mann-Whitney U-tests. Categorical data are described as numbers or percentages and analyzed using Fisher’s exact test or chi-squared test. Univariate repeated measures ANOVA will be used for intra-group comparisons and post hoc tests with Bonferroni correction will be used to control for Type I error. We will perform a Mantel–Haenszel test, stratified according to whether MAP < 55 mmHg occurs during PEEP titration and other possible confounding factors, to compare the risks of POD in each group. *P* values < 0.05 will be considered statistically significant.

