### Trial status

So far, we have recruited 12 participants, and the trial has not been completed participant recruitment at the time of submission. The study will begin in January 2022 and the recruitment phase will last for one year. Protocol version 1.0.

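### As worded, the safety rule suspends the whole trial for any listed adverse event, including hypotension, which the protocol foresees and plans to treat during PEEP titration

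*Protocol article*

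**What the plan says.** Three parts of the protocol article bear on this.

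- **Safety evaluation.** The scope is set first: "The researchers will monitor all adverse events (AEs) associated with the PEEP titration procedure". The list follows: "AEs are defined as hypotension, significant cardiac arrhythmias, pneumothorax, significant disability or incapacity, and even death". Arrhythmia and disability are qualified as significant; hypotension is not qualified. The section ends: "Once AEs occur, the trial will be suspended and an investigation will begin". That sentence sets no condition on seriousness, number, relatedness or expectedness.
- **Interventions.** For the titration period: "If circulatory instability occurs during PEEP titration, intravenous infusion of noradrenaline will be used to maintain MAP ≥ 55mmHg". For anaesthesia in general, in both groups: "Vasoactive drugs will be used to maintain mean arterial pressure (MAP) and heart rate within ± 20% of the baseline".
- **Statistical methods.** The Mantel–Haenszel comparison of delirium risk is to be "stratified according to whether MAP < 55 mmHg occurs during PEEP titration", among other factors.

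Only Group I is titrated, with PEEP stepped from 4 to 16 cm H2O in the prone position.

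**The concern.** Low pressure during titration is an event the authors expect. They name a drug for it and plan to classify patients by it in the analysis. The safety rule gives that event the same trial-level consequence as a death.

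Two outcomes are possible. If staff follow the sentence, one treated episode of hypotension stops the trial until an investigation has been held. If they disregard it for hypotension, they are setting aside the only suspension rule the article states for pneumothorax, disability and death, and when to suspend becomes a case-by-case decision. Neither is what a safety rule should produce.

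**Working it through.** The document states no figure on this point, so there is none to reproduce. The check has two parts.

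**1. The sections side by side**

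| Place | Treatment of low pressure |
|---|---|
| Interventions, titration | Foreseen; noradrenaline to hold MAP at 55 mmHg or above |
| Statistical methods | Foreseen; MAP below 55 mmHg during titration defines a stratum |
| Safety evaluation | Listed as an adverse event without a threshold; any listed event suspends the trial |

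The first two rows treat low pressure as something that happens to individual patients while the trial goes on. The third makes it a trial-level trigger.

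**2. How often the rule could be triggered**

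Inputs:
- Enrolment of 106 (Sample size calculation) and 1:1 allocation (Randomization and blinding) give 106 / 2 = 53 titrated patients.
- The rate *p* of hypotension per titrated patient is not given. A range of 1% to 10% is assumed.
- Each affected patient is taken to cause one trigger, independently of the others.

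Formulas:
- P(at least one) = 1 − (1 − p)^n
- P(two or more) = 1 − (1 − p)^n − n p (1 − p)^(n−1)
- Expected number = n p

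Example at p = 0.02, n = 53: 1 − 0.98^53 = 0.657; expected 53 × 0.02 = 1.06.

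| Assumed p | At least one (n = 53) | Two or more (n = 53) | Expected (n = 53) |
|---|---|---|---|
| 1% | 41.3% | 9.9% | 0.53 |
| 2% | 65.7% | 28.7% | 1.06 |
| 5% | 93.4% | 75.0% | 2.65 |
| 10% | 99.6% | 97.4% | 5.30 |

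**3. Patients an amendment could still reach**

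The Trial status section reports: "So far, we have recruited 12 participants, and the trial has not been completed participant recruitment at the time of submission". That leaves 106 − 12 = 94 patients, about 47 in Group I if split evenly. With n = 47, the chance of at least one halt at 1%, 2%, 5% and 10% is 37.7%, 61.3%, 91.0% and 99.3%, with 0.47, 0.94, 2.35 and 4.70 expected.

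**4. If hypotension in either group counted**

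The stated scope is titration-associated events, so n = 53 is the relevant number. If the scope were widened to both groups and the suspension sentence left alone, n would be 106. With the same assumed rates in both groups, the chance of at least one halt would be 65.5%, 88.3%, 99.6% and above 99.9%. This matters for the fix: the two sentences have to change together.

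**The case against.** **The authors meant stopping the procedure in that patient.** This is possible. The section is otherwise about individual patients, and the Discharge criteria include "interruption of study protocol", which could be how such a patient leaves the study. That criterion fits either reading and settles nothing. But the sentence says the trial is suspended, so on the patient-level reading it still needs correcting.

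**Thresholds and grading belong in the full protocol.** Agreed. The lack of a numerical definition of hypotension is not the point made here. The point is a rule that the article does state.

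**Giving a vasopressor is not the same as having the adverse event.** This stands in part. The Interventions text sets pressure targets, and a small dip corrected within target need not count as hypotension. The general instruction on vasoactive drugs is therefore weak support, more so because the safety section is limited to titration-associated events. The titration instruction and the MAP stratum carry the argument.

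**Caution is for the sponsor and the ethics committee to set.** True, and it is why this is offered as an improvement. Halting for an expected, treated event adds little protection.

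**Stronger readings that the document does not support.** A reader might infer a formal contradiction, in that the MAP stratum could never fill if every such event suspended the trial. That does not follow: a patient can be treated, the trial paused and resumed, and the patient analysed. A reader might also infer lost recruitment, lost power or a biased primary comparison. The document gives neither an event rate nor a suspension length, so none of these can be shown. Nor is a run of repeated halts established: two or more are likely only towards the upper end of the assumed rates.

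**Conclusion.** The point holds as a matter of trial conduct. The stated rule works badly if followed, because a foreseen and treated event triggers a whole-trial halt. At assumed hypotension rates of 1% to 10% in 53 titrated patients, the chance of at least one halt is 41% to 99.6%; at 2% it is already more likely than not. These figures rest on rates the document does not anchor, on one trigger per affected patient, and on the literal reading of the suspension sentence. No effect on the primary endpoint, type I error, power or recruitment is shown. Severity is minor; this is a cheap improvement.

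**What to change.** Change two sentences in Safety evaluation together.

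- **First sentence:** state that all intraoperative and postoperative adverse events will be monitored in both groups, including those associated with PEEP titration. Otherwise recording treated hypotension in both groups would clash with a scope that only Group I can meet.
- **Last sentence, replaced by two:**
  - *Hypotension or arrhythmia during titration will be treated as set out under Interventions; titration will be stopped in that patient if it persists; and it will be recorded as an adverse event without suspending the trial.*
  - *If a serious or unexpected adverse event occurs (pneumothorax, life-threatening arrhythmia, hypotension refractory to treatment, significant disability or incapacity, or death), the trial will be suspended and the event investigated.*

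This gives arrhythmia a defined place on each side of the line and keeps suspension for the events that warrant it. Daily visits and the recording of all events stay as they are.

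Cost: a short amendment reviewed by the ethics committee, as the Protocol amendments section requires, and recording of intraoperative events in Group C as well. No visits are added, since all patients are already seen daily until discharge. The downside is a somewhat less cautious rule for non-serious events.

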## Discussion

POD is a state of acute brain dysfunction, characterized by fluctuating alterations of consciousness, attention, and cognition [20]. As a common postoperative complication of hospitalized elderly patients, POD usually occurs 2–5 days after surgery and it is related to prolonged length of hospital stay and decreased functional independence [2, 21]. Additionally, POD could result in long-lasting cognitive dysfunction even in recovered patients [22]. Therefore, it is of important clinical significance to explore the pathogenesis and prevention measures of POD in elderly patients to prevent POD and promote recovery.

Patients undergoing prone position surgery such as percutaneous nephrolithotripsy or posterior spinal surgery are prone to deterioration of airway pressure, pulmonary compliance, and rSO_2 _[9]. The rSO_2_, an indicator of brain oxygen consumption and supplementation, can predict brain hypoxia [23]. Two main factors may lead to the decrease in rSO_2_ when position changes from supine to prone position [9, 24]. Firstly, caval compression may lead to a reduced cardiac output, which can decrease the perfusion pressure of the brain. Alternatively, the increase of intrathoracic pressure may affect the reflux of cerebral venous blood volume to the right atrium, resulting in an increase in the proportion of cerebral venous blood volume and a decrease in rSO_2_. Previous study has shown that the reduction of intraoperative rSO_2_ may increase the risk of POD [25]. The mechanism may be that reduced oxygen supply to the brain leads to hypoxia and metabolic dysfunction of brain cells, thereby reducing the number of neurons and leading to POD [4].

Inflammation is another major risk factor for POD [26]. Mechanical ventilation could account for VILI and might induce the release of proinflammatory mediators. Due to the decrease of lung compliance in elderly patients, inflammation and VILI are more likely to occur during mechanical ventilation. However, peripheral inflammatory factors can exacerbate the inflammation of the brain and contribute to neuronal injury [27]. Proinflammatory markers such as IL-1β and IL-6 could trigger neuroinflammation and may be associated with cognitive decline [28, 29]. Surgical patients undergoing prone positions tend to have increased airway pressure and decreased pulmonary compliance, which could lead to inflammation response and lung injury [4]. Therefore, appropriate ventilation strategies may be useful to prevent VILI and POD.

A recent study has shown that POD can be prevented by employing intraoperative lung-protective ventilation consisting of V_T_ of 6 ml/kg PBW and PEEP of 5 cm H_2_O in elderly patients undergoing posterior spinal surgery in prone position[4]. Lung-protective ventilation, consisting of a low tidal volume, recruitment maneuvers, and moderate PEEP, has been found to effectively decrease the incidence of PPCs [30]. Meanwhile, lung-protective ventilation is an appropriate way of reducing the systemic proinflammatory response because of the use of a moderate PEEP and the reduction of tidal volume [31]. Previous studies demonstrated that the application of PEEP could improve rSO_2 _[4, 13]. However, applying a low V_T_ with a fixed or insufficient PEEP for all patients is inappropriate because this may lead to atelectrauma [32]. Our team found that employing individualized PEEP can improve oxygenation and reduce inflammatory markers compared with fixed PEEP strategies in patients undergoing thoracoscopic and laparoscopic surgery [11, 12]. Hence, we assume that individualized PEEP can prevent POD among elderly surgical patients in prone position by increasing rSO_2_ and reducing inflammation.

This study has two main limitations. First, all patients will be recruited from a single center. Second, the sample size of this trial is limited and a larger clinical trial is needed. To sum up, the trial is hopefully to replenish new clinical evidence for individualized PEEP to prevent POD in surgical elderly patients undergoing prone position.

### Trial status

So far, we have recruited 12 participants, and the trial has not been completed participant recruitment at the time of submission. The study will begin in January 2022 and the recruitment phase will last for one year. Protocol version 1.0.

## Data Availability

The datasets used and/or analyzed during the current study are available from the corresponding author on reasonable request.

## Abbreviations

AEs: adverse events
BIS: bispectral index
CAM: Confusion Assessment Method
Cdyn: dynamic compliance
FIO_2_: fraction of inspired oxygen
LUS: lung ultrasound score
MAP: mean arterial pressure
NIBP: Noninvasive blood pressure
NIRS: near-infrared spectroscopy
NSE: neuron-specific enolase
PACU: postanesthesia care unit
PBW: Predictive body weight
PCIA: intravenous patient-controlled analgesia
PCV-VG: pressure‑controlled ventilation‑volume guaranteed
PEEP: Positive end-expiratory pressure
P_ET_CO_2_: end-tidal carbon dioxide
P_mean_: mean airway pressure
POD: Postoperative delirium
P_peak_: Peak airway pressure
RM: Recruitment maneuvers
rSO_2_: Cerebral oxygen saturation
VILI: Ventilator-induced lung injury
V_T_: tidal volumes
